## Abstract

**Background:**

Epidemiological studies suggest that compared with the general population, mood disorders are up to 4.7 times more prevalent in substance dependent samples. Comorbid substance use disorder (SUD) and depression has been associated with a more severe and protracted illness course and poorer treatment outcomes. Despite this, the development and assessment of behavioural interventions for treating depression among individuals with SUDs have received little empirical attention. Behavioural Activation Treatment for Depression (BATD-R) is an empirically supported treatment for depression that has shown some efficacy among substance users. This paper describes the study protocol of a parallel, single blind, randomised controlled trial to determine the efficacy and feasibility of a modified version of the BATD-R (Activate) in reducing symptoms of depression and substance dependence among individuals in residential rehabilitation (RR) and opioid substitution therapy (OST).

**Methods/design:**

A sample of approximately 200 individuals with depressive symptomatology in treatment for SUD will be recruited from RR and OST services in New South Wales, Australia. Dynamic random allocation following minimisation methodology will be used to assign participants to one of two groups. The control group will receive treatment as usual (TAU), which will be the model of care provided in accordance with standard practice at participating RR and OST services. The intervention group will receive Activate, comprising 10 individual 60-min therapy sessions with a psychologist employed on the research team, in addition to TAU. Data collection will occur at baseline (pre-intervention), and 3-months and 12-months post baseline.

**Discussion:**

The association between depression and substance dependence has been well documented, yet practical and effective treatments are scarce. The findings of the present study will contribute significantly to understanding the types of programs that are effective in treating this comorbidity.

**Trial registration:**

This trial is registered with the Australian and New Zealand Clinical Trials registry, ACTRN12613000876796. Registered on 7 August, 2013.

**Electronic supplementary material:**

The online version of this article (doi:10.1186/s12888-016-0943-1) contains supplementary material, which is available to authorized users.

## Background

The frequent co-occurrence of depression and substance use disorders (SUDs) is well documented both in Australia and internationally [1–9], with epidemiological studies suggesting that affective disorders are up to 4.7 times more prevalent among substance dependent samples compared to the general population [10–12]. Particular cause for concern is the high prevalence of current major depression among treatment seeking substance users, with studies reporting rates as high as 20–55 % [2, 4, 13–15]. Despite evidence that depression is linked to poorer treatment outcomes [16–20], the development and assessment of behavioural interventions for depression among substance users has received little empirical attention.

### Impact of depression on treatment for drug dependence

Among substance users, depression has been associated with a more severe and protracted illness course, poorer social and occupational functioning, greater use of health services, an increased risk of post-traumatic stress disorder, higher risk of suicidal behaviours, and an increased risk of relapse in substance use problems [20–22]. The Australian Treatment Outcome Study (ATOS), a longitudinal study of treatment outcomes for heroin dependence, demonstrated that across a 3 year follow-up period clients who met DSM-IV criteria for major depression in the month preceding interview were more likely to be using heroin and other drugs, to be heroin-dependent, sharing needles, experiencing injection-related health problems, engaging in crime and were in poorer physical and mental health than non-depressed clients [20]. Depression was the only consistent predictor of poorer treatment outcome across the 3 year period [20]. Clearly, co-occurring depression and SUDs presents a complex clinical challenge for treatment providers that requires further empirical attention.

Depression and SUDs, when considered as separately occurring disorders, can be attributed to a number of environmental, genetic and neurobiological factors. In contrast, the mechanisms underlying these conditions as they co-occur are not well understood [23]. Four main hypotheses have been proposed to explain this comorbidity [24]. The self-medication hypothesis suggests that substance dependence occurs as a result of repeated substance use aimed at relieving the symptoms of depression. Secondly, depressive symptoms may develop as a direct result of taking substances or as part of withdrawal symptoms when substance use stops (e.g. substance-induced depression). Thirdly, depressive symptoms may develop in response to the lifestyle associated with using substances. Alternatively, both disorders may share common psychological or biological antecedents, thereby increasing the likelihood that they will co-occur. Regardless of which disorder came first, once co-occurring SUD and depression has been established, each may act to maintain or exacerbate the other [24].

### Current treatment protocols for co-occurring depression and SUDs

While treatment has traditionally been determined based on the temporal relationship between depression and SUDs (i.e., treating the disorder with the earlier onset first), there are practical difficulties in reliably diagnosing primary and secondary conditions [25]. It has been suggested that the primary/secondary distinction is immaterial once depression and SUDs have surfaced [26], and that the focus of treatment should be on the impairment and distress caused by symptoms, as opposed to diagnostic sub-type classification, or the model of aetiology [27].

There is some evidence, albeit limited, for the effectiveness of cognitive behavioural therapy (CBT) either alone or in combination with antidepressant use for the treatment of co-occurring depression and SUDs [28]. Unfortunately, however, only a handful of methodologically sound studies have been conducted to date, and these have focused on alcohol use outcomes, with limited reports on other substance use outcomes. While there is support for the use of CBT in the treatment of depression and co-occurring tobacco [29] and alcohol dependence [30], there are a number of difficulties when implementing depression focussed CBT treatment in a population dependent on a variety of licit and illicit substances, as outlined by Daughters and colleagues [31]. CBT focuses on complex cognitive techniques, which may be too cognitively challenging for chronic substance users with cognitive deficits and low education levels [32, 33]. Its time-consuming nature makes it difficult to incorporate into existing substance abuse treatments [34] and it requires a high level of training in complex therapy based treatments, which staff may not be able to deliver in traditional drug and alcohol treatment settings [35].

### Behavioural activation

A treatment that may be better suited for use among substance users is behavioural activation. According to this approach, symptoms and behaviours characteristic of depression arise when susceptible people experience problems that significantly reduce their ability to gain positive reward from their environment [36]. Behavioural activation is a structured treatment for depression designed to activate clients in ways that are tailored to increase rewarding experiences in their lives [36]. It is an action oriented approach that requires between session practice by clients, with therapists and clients working collaboratively to develop activation tasks for clients to complete outside the session and trouble-shoot obstacles that may arise. Empirical evidence suggests that behavioural activation therapy is just as effective as CBT [37, 38], and is more time efficient and less complex when compared to most other treatments for depression [39]. Behavioural activation therapy has been shown to be an efficacious, cost-effective alternative to cognitive therapy and antidepressant medication [40, 41].

Behavioural Activation Treatment for Depression (BATD) [39] is a brief manualised treatment which employs activity scheduling and other behavioural techniques within a framework applying matching law [42] to understand depression. This law suggests that depression persists when (a) reinforcement available for non-depressed (healthy) behaviour is low or non-existent, or (b) depressed (unhealthy) behaviour provides a relatively high degree of reinforcement [39]. Depression is therefore seen as the result of both decreased reinforcement for non-depressed, healthy behaviours, and increased reinforcement for depressed behaviours [43]. The structured BATD protocol seeks to increase non-depressed behaviour by providing exposure to the positive consequences of healthy behaviour, and has shown promise in treating depression among substance users [31, 44]. The manual was recently revised ([BATD-R; [45]), to improve delivery and patient acceptability.

### Evidence base for BATD

Lead developers of the manual, [name] and Hopko, first pilot tested BATD among psychiatric inpatients suffering depression, and yielded a large pre-to-post treatment effect size (*d* = .73) for depression symptoms [46]. BATD gained additional support from three small randomised controlled pilot trials [31, 44, 47]. Daughters and colleagues (2008) added a behavioural intervention for depression (BATD) to inpatient treatment for illicit drug use (Lets Act!; *N* = 44) [31]. Those who received the Lets Act! intervention had significantly greater improvements in depression at post-treatment and 2-week follow-up compared with standard care alone. A subsequent trial compared Lets Act! with a time matched control treatment (supportive counselling), and found that while both groups showed a significant reduction in depressive symptoms on completion of treatment, retention in drug treatment was significantly greater in the behavioural activation group [44]. No follow-up data was collected beyond treatment completion. Another randomised controlled trial (*N* = 68) involving adult smokers with mildly elevated depressive symptoms and seeking smoking cessation treatment, found that participants allocated to ‘Behavioral Activation Treatment for Smoking (BATS)’, which was adapted from BATD, reported greater smoking abstinence, and a larger reduction in depressive symptoms at 16- and 24-week follow-up, than those who received standard smoking cessation treatment [47].

While the results of these trials are promising, and suggest preliminary support for the feasibility, acceptability and efficacy of brief behavioural activation treatment for improving mood and substance use outcomes, further research is needed. BATD-R was initially developed for use in the United States (US) and its efficacy has not been assessed in drug treatment services outside the US, among substance users in outpatient drug and alcohol treatment settings, or over long-term follow-up (i.e., 12-months) in either residential or outpatient drug treatment settings. The three clinical trials conducted to date have also all used a group rather than individual format.

## Methods/design

### Trial aims & hypotheses

The primary aim of the proposed trial is to determine the efficacy of a modified version of BATD-R (Activate) in reducing depressive symptoms among individuals with SUDs who are currently undergoing Residential Rehabilitation (RR) or Opioid Substitution Therapy (OST). It is hypothesised that:Participants who receive Activate will demonstrate greater reductions in symptom severity for (i) depression and (ii) substance dependence, 3- and 12-months post baseline, compared to those who only receive treatment as usual.Activate will be a feasible approach to treating comorbid depression and substance dependence, as measured by treatment retention and client satisfaction.

The secondary aim of the trial is to investigate the impact of other factors that may moderate or mediate the Activate treatment response. Secondary outcome measures will include those related directly to the therapy (environmental reward, behavioural activation), and those concerned with mental health (anxiety symptoms, social phobia, borderline personality disorder, traumatic events, rumination, distress tolerance, suicide history and sleep).

### Trial design

The Activate study is a parallel, single blind, superiority randomised controlled trial. Participants will be randomly assigned to receive either Activate (*n* = 100) or treatment as usual (TAU; *n* = 100), stratified by treatment modality (RR and OST). Treatment as usual is the comparator group, as it is clinically important to determine whether Activate adds any benefit in terms of improved depression symptomatology and reduced dependence symptoms, beyond that gained from usual care (i.e. RR or OST). Separate randomisation schedules will be used for the two treatment modalities. To reduce the risk of bias, minimisation, a dynamic random allocation technique, will be completed by someone independent of the research team using Minim-Py [48]. Gender and depression severity have been identified as significant prognostic factors and minimisation will ensure classification of participants with respect to these variables. Depression severity will be categorised according to BDI-II score, as mild (14–19), moderate (20–28) or severe (29–63) [49]. Minimisation has been shown to have both theoretical and practical validity, in particular it is considered an effective randomisation tool in clinical trials of small to moderate sample size (approximately, *N* = 200–400) with multiple prognostic factors to be considered [50–52].

The National Health and Medical Research Council of Australia (NHMRC) provided a project grant (#10444625) enabling the Activate study to be conducted. The funding period was initially February 2013 to December 2015, but was extended to December 2016 to accommodate extension of the baseline recruitment phase. Ethics approval was obtained from the University of New South Wales Human Research Ethics Committee (HREC) (Ref No: HC13155), and the Northern Sydney Local Health District HREC (Ref No: HREC/12/HAWKE /404). A model of the information and consent form used is available as supplementary material (Additional file 1). The study has been prospectively registered in the Australian and New Zealand Clinical Trials Registry (ACTRN12613000876796, 7/08/13). Any changes to the trial protocol which may impact the conduct of the study, the benefit to the patient or patient safety, will require a formal amendment to the protocol. Approval for such amendments will be sought from the HRECs and the trial registry will be updated. See Table 1 for the WHO Trial Registration Data Set. Additional information regarding groups overseeing the trial, insurance coverage, and authorship guidelines can be found in the supplementary material (Additional file 1).

**Table 1 Tab1:** Trial registration data set as recommended by the World Health Organization (WHO)

Data category	Information
Primary registry and trial identifying number	Australian and New Zealand Clinical Trials registry, ACTRN12613000876796
Date of registration in primary registry	7 August, 2013
Secondary identifying numbers	Universal Trial Number U1111-1142-2213
Source(s) of monetary or material support	National Health and Medical Research Council
Primary sponsor	National Drug & Alcohol Research Centre, University of New South Wales, Sydney, NSW 2052
Contact for public queries	[name] ([contact])
Contact for scientific queries	[name] National Drug & Alcohol Research Centre, UNSW, Sydney, Australia
Public title	Treatment for depression among people with substance use disorder: The Activate Study
Scientific title	The efficacy of behavioural activation therapy for co-occurring depression and substance use disorder: The Activate Study
Countries of recruitment	Australia
Health condition(s) or problem(s) studied	Depression and Substance Use Disorder
Intervention(s)	The intervention is Behavioral Activation Treatment for Depression (BATD-R), modified for use in outpatient and in-patient drug and alcohol treatment settings (Activate). Comparator: Treatment as usual i.e. Residential Rehabilitation (RR) or Opioid Substitution Treatment (OST).
Key inclusion and exclusion criteria	Inclusion criteria: a) 18 years of age or older b) Literate in English c) Willing to give locator information d) Entered RR within the last month or in OST for at least 3 months e) Endorse CIDI 3.0 depression screening criteria f) Score at least in the mild range on PHQ-9 g) Substance use in the month prior to interview Exclusion criteria: a) Active suicidality b) Active psychosis c) Organic or traumatic brain injury d) Not living in the greater Sydney metropolitan area e) Not living in the community in the month prior to baseline
Study type	Interventional. Allocation: randomised; intervention model: parallel assignment; Masking: the research officers assessing outcomes are blind to the allocation Primary purpose: Treatment
Date of first enrolment	12/08/2013
Target sample size	200
Recruitment status	Recruitment completed. Analysis ongoing.
Primary outcome(s)	1) Depression Severity - Beck Depression Inventory (BDI-II) score - Composite International Diagnostic Interview 3.0 (CIDI) assessment of Major Depression. 2) Substance Use Disorder - CIDI assessment of substance use disorder - Severity of dependence scale (SDS)
Key secondary outcomes	1) Treatment feasibility as assessed by treatment retention and client satisfaction (assessed using the Client Satisfaction Questionnaire on completion of the Activate intervention) 2) Factors that influence the efficacy of the modified BATD-R (Activate) including client and treatment characteristics (assessed at baseline, 3 and 12 months).

Date and version identifier: Issue date: 17 Feb 2016

Protocol amendment number: 01 Authors: KP, JR

Revision chronology:

00, 7 August, 2013 Original

01, 17 February, 2016 Amendment 01.:

Two exclusion criteria, i.e. d) not living in the greater Sydney metropolitan area and e) not living in the community in the month prior to baseline, were added, as omitted from the original list

Actual date that the first participant entered the study was added (12.08.13)

Date of last participant enrolment was changed from 3.12.14 to 26.02.15. The baseline recruitment phase was extended due to delays with ethics and to help boost recruitment

List of recruitment sites was updated

File updated to indicate that Ethics Approval was obtained from Northern Sydney Local Health District HREC on 4 December 2013

#### Sample size calculation

Power analysis on the primary outcome variables (i.e., severity of dependence and depressive symptoms) was conducted using Power Analysis and Sample Size software [53]. Based on previous research, including the longitudinal study of treatment outcomes for heroin dependence (ATOS; [20]), an exchangeable working correlation matrix and a within-subject correlation of ρ^1^ = .60 for dependence and ρ^1^ = .023 for depression was assumed. The proposed final sample size of 160 will allow for the detection of clinically meaningful differences between the treatment and control groups. Specifically, it will allow for the detection of a time-averaged difference of 3 in severity of substance dependence with a standard deviation of 5 (β = 99 % power; *α* = 0.05); a 15 % difference in the prevalence of substance dependence (β = 96 % power; *α* = 0.05); a difference of 5 in BDI-II scores with a standard deviation of 15 (β = 81 % power; *α* = 0.05); and a 15 % difference in the prevalence of major depression (β = 93 % power; *α* = 0.05). To allow for an expected attrition rate of 20 %, the initial sample will be 200, with the aim of recruiting 50 % of participants from RR and 50 % from OST.

Participants will be 18 years of age or older, literate in English, willing to give locator information, and must have been in RR for at least 1 week or OST for at least 3 months. RR clients must have used a substance (i.e., alcohol, methamphetamines, cannabis, cocaine, hallucinogens, illicit benzodiazepines, heroin or other opiates/opioids) at least four times in the month prior to detoxing, and OST clients must have used a substance at least four times in the past month. If alcohol is the only substance used, individuals need to have consumed four or more standard drinks on at least 4 days in the month before detoxing/past month. The depression screening criteria from the Composite International Diagnostic Interview 3.0 (CIDI; [54, 55]) must be endorsed, indicating that the individual has experienced symptoms of depression that persisted for 2 weeks or longer in the month before detoxing/past month, and these symptoms must be ongoing. Depression symptom severity will be assessed using the Patient Health Questionnaire (PHQ-9; [56]), with a score in the mild to severe range (i.e., 5–27) required to be eligible for the study.

Active suicidality, psychosis and organic or traumatic brain injury will exclude an individual from entering the study. Suicidality is assessed by the PHQ-9 during the screening interview. Participants are asked “in the past 2 weeks/2-weeks before detox, have you been bothered by thoughts that you would be better off dead.” If participants indicate that they have been bothered by these thoughts, the research officer then probes further, using questions taken from the Suicide Assessment Kit screener [57], to determine whether these thoughts are ongoing, how long they have been having the thoughts, how intense they are, how likely it is that they will act on these thoughts in the near future, whether they have ever attempted suicide previously, and if so, how recently. Individuals who have attempted suicide in the past 6 months and for whom nothing has changed (i.e., they have received no intervention, or nothing has changed in their circumstances to reduce their risk), will be excluded from the study, and given a referral for appropriate support. If the thoughts are intense or the participant deems it likely that they will act on them in the near future, they are asked about any current plans and prior attempts, and are referred to an appropriate staff member at the treatment service for ongoing support and management.

Suicidality is assessed further as part of the baseline interview. The BDI-II and CIDI 3.0 both ask questions about suicidal thoughts, with the CIDI also asking about plans and attempts [49, 55]. Additional questions about the lifetime number of suicide attempts and recency of the last attempt are also asked. In situations where suicidality is indicated, the research officer uses the additional probing questions described above to assess their current risk, and to determine whether there is a need for exclusion from the study and referral for additional support. It is possible for a person with a current plan and thoughts of suicide to be recruited to the study provided the risk is not deemed imminent, and the treatment service is made aware of the suicidal thoughts and plan.

As part of the screening questionnaire, potential participants are asked whether they have ever been diagnosed with bipolar, mania, or schizophrenia. If the response is yes, (or if the individual reports being prescribed antipsychotics during the baseline interview), the project psychologist will meet briefly with them and ask them whether they ever see or hear things that other people cannot see or hear, whether the hallucinations are believed to be drug induced, whether the hallucinations are current, and how these are managed. These individuals are also asked about having unusual thoughts or beliefs. The psychologist then makes a clinical decision about their eligibility for the study. Self-report of having received a diagnosis of traumatic brain injury, as ascertained during the screening interview, is also a reason for exclusion.

Exclusion from the study in all of the above cases is based on the individual’s inability to effectively engage with, and thus benefit from, the type of intervention offered. Decisions to exclude on the basis of suicidality, psychosis or traumatic brain injury will all be made in consultation with the project coordinator and/or a project psychologist prior to randomisation. Alternate referral for treatment will be provided where necessary. Additionally, for reasons of feasibility in providing the Activate intervention and contacting participants for follow-up, clients will be excluded if they do not live in the Greater Sydney Metropolitan, Central Coast or Hunter New England regions. To ensure that participants have been at liberty to use substances in the month prior to detox or past month, individuals not living in the community (e.g., incarcerated) during that period will be excluded.

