#### Primary outcome measures

Depression: The severity of depression symptoms in the past 2 weeks will be assessed using the 21-item Beck Depression Inventory (BDI-II; [49]). Each item comprises a list of four statements arranged in increasing severity about a particular symptom of depression. Scores range from 0 to 63, with higher total scores indicating more severe depressive symptoms. Depression can then be interpreted as minimal (0–13), mild (14–19), moderate (20–28), or severe (≥29). The BDI-II has been widely used in both clinical and non-clinical studies, has shown good test-retest reliability (Pearson’s *r* = .73-.96), and high internal consistency (Chronbach’s α = .83-.96) [59]. A past month diagnosis of major depression will be ascertained by completing the CIDI 3.0 depression section, modified to assess the presence of symptoms in the past month [54, 55]. The CIDI 3.0 major depression module has been found to have moderate concordance with the Structured Clinical Interview for DSM (SCID) (area under the receiver operator curve; AUC = 0.75) [60].

Substance Dependence: Psychological components of dependence will be measured using the Severity of Dependence Scale (SDS; [61]). Each of the 5 items is scored on a 4-point scale, ranging from 0 to 3. A total score is obtained, with higher scores indicating a higher level of dependence. The inter-item reliability has been demonstrated across five drug using samples, with Cronbach’s alpha values ranging between 0.8 and 0.9 [61]. A diagnosis of substance dependence will be established using the CIDI 3.0, with the number of dependence criteria endorsed (0–7) being used as an indicator of severity [54]. The CIDI 3.0 substance use disorder module has been found to have moderate concordance with the SCID (Alcohol dependence, AUC = 0.72; Drug dependence, AUC = 0.62) [60].

Problematic alcohol use will be screened for using the 4-item CAGE questionnaire [62]. Scores range from 0 to 4, with scores greater than or equal to 2 considered to be clinically significant. The CAGE has demonstrated high test-retest reliability (*r* = 0.80–0.95), and adequate correlations (*r* = 0.48–0.70) with other screening instruments such as the Alcohol Use Disorders Identification Test (AUDIT) and Short Michigan Alcohol Screening Test (SMAST) [63].

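### The stated 81% power for BDI-II does not follow from the stated inputs, and the within-subject correlation of .023 needs a source or a correction

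*Protocol article*

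**What the plan says.** The protocol article, under Sample size calculation, bases the power analysis on "an exchangeable working correlation matrix and a within-subject correlation of" .60 for dependence and .023 for depression, citing previous research that includes a heroin-treatment cohort. From just after the decimal point of the second value, the text runs: "023 for depression was assumed. The proposed final sample size of 160 will allow for the detection of clinically meaningful differences". For depression severity the target is "a difference of 5 in BDI-II scores with a standard deviation of 15", with power given as 81% at alpha 0.05. The text does not give the sidedness of the test or the number of repeated measures entered.

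Three other statements bear on the value .023:

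- Trial design: "Gender and depression severity have been identified as significant prognostic factors". BDI-II severity bands are used in the minimisation.
- Primary outcome measures: the BDI-II "has shown good test-retest reliability", with Pearson r of .73 to .96.
- Assessment occasions: primary outcomes are measured at baseline, 3 months and 12 months, and the baseline interview precedes randomisation.

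The Statistical analysis section plans mixed or marginal longitudinal models and does not say whether baseline BDI-II is a covariate.

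**The concern.** There are two problems. First, the inputs and the output of the BDI-II power statement do not match, so a reader cannot tell which calculation supports 160 completers for a primary outcome.

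Second, a correlation of .023 means that one BDI-II score shares .023² = 0.05% of its variance with another score from the same person. In a comparison of averages over visits, such a low value is favourable: each additional visit counts almost as a new participant. If the true correlation is much higher, the unadjusted comparison has less power than the stated inputs imply. Depressive symptoms are the primary aim, so the assumption needs to be visible and defensible.

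**Working it through.** **Inputs.** Final N = 160, difference 5, SD 15, alpha 0.05, correlation ρ = .023, exchangeable (Sample size calculation). Equal allocation (Trial design), hence 80 per arm. Two assumptions are added: a two-sided test, and a time-averaged difference for BDI-II, a term the protocol attaches only to the dependence score.

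**Formula, no baseline adjustment.** With m occasions the variance factor is F = (1 + (m − 1)ρ)/m. Then SE = SD × √(F × 2/80) and power = Φ(difference/SE − 1.96).

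**Does the method reproduce a figure in the plan?** For dependence (difference 3, SD 5, ρ = .60):

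- m = 2: F = .80, SE = 0.707, power = Φ(4.243 − 1.96) = 98.9%
- m = 3: F = .733, SE = 0.677, power = Φ(4.431 − 1.96) = 99.3%

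The protocol states 99%, so the formula is plausibly the one that was used.

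**BDI-II at ρ = .023:**

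- m = 1: F = 1, SE = 2.372, power = Φ(2.108 − 1.96) = 55.9%
- m = 2: F = .5115, SE = 1.696, power = Φ(2.948 − 1.96) = 83.8%
- m = 3: F = .3487, SE = 1.400, power = Φ(3.570 − 1.96) = 94.6%

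None is 81%. Variations do not recover it:

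- A noncentral t calculation gives 83.4% for m = 2.
- One-sided tests give 67.8%, 90.4% and 97.3% for m = 1, 2 and 3.
- Using all 100 per arm gives 65.4%, 90.9% and 97.9%.
- Reading .023 as a misprint of .23 gives 76.7% (m = 2) or 85.6% (m = 3).

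Solving for 81% at 80 per arm gives ρ of about .10 (m = 2) or .33 (m = 3). Keeping ρ = .023 and m = 2, it takes 74 or 75 per arm.

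**Sensitivity to ρ.** The range .3 to .6 is an assumption; the protocol gives no BDI-II correlation over 3 to 12 months. For the baseline-adjusted analysis the variance factor is (1 + ρ)/2 − ρ² for the average of two follow-ups, and 1 − ρ² for one visit. Both take the baseline-to-follow-up correlation to be ρ as well.

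| ρ | Two follow-ups, unadjusted | Three occasions, unadjusted | Two follow-ups, baseline-adjusted |
|---|---|---|---|
| .3 | 74.4% | 82.3% | 80.4% |
| .5 | 68.2% | 73.3% | 84.6% |
| .6 | 65.4% | 69.2% | 88.8% |

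Single baseline-adjusted visit:

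- ρ = .3: F = .91, SE = 2.262, power = Φ(2.210 − 1.96) = 60%
- ρ = .6: F = .64, SE = 1.897, power = Φ(2.635 − 1.96) = 75%

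**Unequal correlations.** If baseline correlates .3 with each follow-up while the follow-ups correlate .6 with each other (again an assumption), F = .80 − .09 = .71, SE = 1.998 and power = Φ(2.502 − 1.96) = 71%.

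**The case against.** The strongest defence has four parts.

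1. **Nothing in the protocol directly contradicts .023.** Test-retest reliability describes the instrument; it is not a correlation over 3 to 12 months in people under treatment who were selected for current depression. Severity is called prognostic without a strength or a time horizon. The .60 belongs to another construct. The value .023 is attributed to earlier research that is not at hand. All of this stands, so the right description is strong tension, not contradiction.
2. **The stated 81% is lower than the longitudinal calculation gives at .023**, and with three occasions and ρ of about .33 it would be right. A reader might infer that the power was overstated, or that it rests on .023. The documents support neither, since .023 does not produce 81%. The three-occasion reading does, however, count the pre-randomisation baseline among the averaged outcomes.
3. **A shortfall to 65–74% depends on choices the protocol does not make.** It takes ρ from an assumed range, two follow-ups and no baseline adjustment. The planned models allow baseline as a covariate, and leaving the covariate list to an analysis plan is normal. A reader should therefore not conclude that the trial is underpowered.
4. **The 93% for major depression cannot be checked.** It is tempting to say that it inherits the same correlation problem, but no base prevalence is given.

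None of this explains why the stated inputs and the stated 81% disagree.

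**Conclusion.** The point holds as a mismatch in a stated figure. Assuming a two-sided, time-averaged comparison with 80 per arm, the BDI-II power at ρ = .023 differs from the stated value by about 3 percentage points with two follow-ups and about 14 with three occasions. At a single time point it is about 25 points lower than stated. The dependence figure reproduces by the same method, so the problem is specific to the BDI-II line.

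That .023 is implausibly low is a judgement from the protocol's other statements, and its consequence for power is conditional on an assumed range for ρ. Baseline adjustment largely removes the conditional shortfall for the averaged comparison. It would go too far to say that it secures 80% at any correlation, because that requires the baseline-to-follow-up correlation to equal the one between follow-ups.

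This should be corrected, but it does not call for a different sample size.

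**What to change.** - Give the source of .023 and the interval to which it applies, or correct it.
- Restate the BDI-II power with the number of occasions, the sidedness of the test and a sensitivity range for ρ, so that it can be reproduced.
- Include baseline BDI-II as a continuous covariate in the planned longitudinal model of the 3- and 12-month scores. Report the power of that analysis, stating the assumption about the baseline-to-follow-up correlation and what happens if it is lower.
- Because the hypothesis names 3 and 12 months, state also that a single baseline-adjusted time point has about 60–75% power for ρ of .3 to .6.

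The cost is a rewritten power paragraph and one sentence on the analysis. Table 1 records recruitment as completed, so N stays as it is, and baseline BDI-II is already in the assessment schedule. The price is a less favourable power statement for single time points.
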